## 6.3 Assessing Adverse Events for Relationship to Study

Any AE that occurs in a subject will be assessed for its relationship to the study. A causal relationship means a drug caused (or is reasonably likely to have caused) the AE. This usually implies a relationship in time between one or more drugs/study agents and the AE—for example, the AE occurred shortly after the subject received the drugs/study agents.

For all AEs, the clinician who examines and evaluates the subject will determine the AE's causality based upon the temporal relationship to administration of the study agents, the pharmacology of the study agents, and his/her clinical judgment.

The following scale will be used to reflect the PI's judgment as to the relationship between the study agents and the AE:

***Definitely Related:*** The AE is clearly related to one or more of the study agents – follows a reasonable temporal sequence from administration of one or more of the study agents, follows a known or expected response pattern to the one or more of the study agents that is confirmed by

improvement on stopping and reappearance of the event in repeated exposure and that could not be reasonably explained by the known characteristics of the subject's clinical state.

***Probably Related:*** The AE and administration of the study agents are reasonably related in time and/or follows a known pattern of response, and the AE is more likely explained by one or more of the study agents than other causes.

***Possibly Related:*** AE follows a reasonable temporal sequence from administration of the study drugs, follows a known or expected response pattern to the suspected drug or drugs, but that could readily have been produced by a number of other factors.

***Unlikely Related:*** A potential relationship between one or more of the study agents and the AE could exist (i.e., the possibility cannot be excluded), but the AE is most likely explained by causes other than one or more of the study agents (e.g., could readily have been produced by the subject's clinical state or could have been due to environmental or other interventions)

***Unrelated:*** AE is clearly not related to one or more of the study agents – another cause of the event is most plausible and/or a clinically plausible, temporal sequence is consistent with the onset of the event and the study medication administration and/or event is biologically implausible.

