## **7.7 Study Sites AE Reporting**

Since the subjects on this protocol will be seen because of illness, and are likely to be ill at baseline, many will have AEs by the above criteria. However, their medical management will be standard of care for those illnesses and complications and not part of the research process. Therefore, AEs associated with the underlying disease will not be recorded as AEs. However, AEs assessed to be related to the research will be recorded as such. As described below, all SAEs will be recorded and reported.

Any grade 3 or 4 AE (as defined in Section 7.1) that is possibly, probably or definitely related to study drugs and occurs between the times a subject signs the informed consent form and the time s/he completes the planned surgery (or at the time of early discontinuation of the subject from study participation for any reason) will be captured and recorded and reported with continuing annual review.

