#### **7.9.1.2 Annual Reporting to the NIAID IRB**

The following items will be reported to the NIAID IRB in summary at the time of Continuing Review:

- All unanticipated problems, including AEs and non-AEs
- Expected serious adverse events that are possibly, probably, or definitely related to the research
- Serious adverse events that are not related to the research
- All protocol deviations which in the opinion of the investigator should be reported.
- Any trends or events which in the opinion of the investigator should be reported

(Protocol violations and deviations mentioned above are defined in the monitoring entity policy.)

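### Section 6.3 lists timing that fits dosing as a ground for rating an adverse event Unrelated, the reverse of the section's own causality principle

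*Protocol*

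**What the plan says.** Protocol section 6.3 opens its account of causality with timing: "This usually implies a relationship in time between one or more drugs/study agents and the AE". The clinician is to judge each event on its timing relative to dosing, the pharmacology of the agents and clinical judgment, using a five-level scale.

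Two of the related levels state the time criterion as follows:
- Probably Related: "The AE and administration of the study agents are reasonably related in time"
- Possibly Related: "AE follows a reasonable temporal sequence from administration of the study drugs"

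Definitely Related also asks for a reasonable sequence in time after dosing.

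The lowest level, Unrelated, begins "AE is clearly not related to one or more of the study agents". It then explains this by three grounds: another cause is the most plausible, and/or "a clinically plausible, temporal sequence is consistent with the onset of the event and the study medication administration", and/or the event is biologically implausible.

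The rating feeds the reporting rules. Section 7.7 captures grade 3 or 4 events that are "possibly, probably or definitely related to study drugs". Sections 7.8 and 7.9.1.1 require SAEs with such a rating to reach the NIAID IRB within 7 days. Section 7.9.1.2 places "Serious adverse events that are not related to the research" in the summary at continuing review.

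**The concern.** A causality scale works only if each criterion points the same way at every level. Here, timing that fits dosing counts towards relatedness in three categories and against it in a fourth. Because the grounds are joined by and/or, the sentence as printed lets the timing ground stand without the other two.

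Timing also carries much of the weight in this trial. Section 6.6.1 says each study drug is given once unless it is already part of the subject's regimen. Definitely Related asks for improvement on stopping and recurrence on re-exposure, which a single dose cannot normally show. That leaves Probably and Possibly Related as the usual routes to a related rating, and both refer to timing.

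At stake is whether an event that merits a related rating could be placed below the threshold that triggers recording or 7-day reporting. Three sites would also be working from a scale that does not agree with itself.

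**Working it through.** No arithmetic applies. The check sets the definitions side by side and then traces which rules depend on the rating.

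**Step 1: direction of the time criterion within section 6.3**

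| Place in 6.3 | Role of timing that fits dosing |
|---|---|
| General principle | Supports causality |
| Definitely Related | Supports relatedness |
| Probably Related | Supports relatedness |
| Possibly Related | Supports relatedness |
| Unlikely Related | Not stated |
| Unrelated | Listed as a ground for no relationship |

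Only the last row is reversed.

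**Step 2: overlap.** Take an event that follows dosing after a plausible interval, fits a known reaction to one of the drugs, and could also have other causes. It meets Possibly Related. It also meets the second ground of Unrelated. The explanatory text therefore does not separate the two categories; only the opening words of Unrelated do.

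**Step 3: rules that depend on the rating**
- Recording of non-serious events (7.7). For grade 3 or 4 events the capture period runs from consent to completion of the planned surgery, or to early discontinuation. Captured events are reported with the annual review, so what is at risk is the record and the annual report, not an expedited report.
- 7-day SAE reports to the NIAID IRB (7.8, 7.9.1.1).
- Unanticipated problems, also a 7-day report (7.9.1.1). The definition in 6.1 requires the problem to be at least possibly related.
- NMC reporting to its own IRB (7.9.5), which is introduced in terms of events related to the study design, intervention or agent.

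**Step 4: rules that do not depend on the rating**
- All SAEs are recorded and reported (7.7).
- Deaths go to the NIAID IRB within 7 days (7.9.1.1).
- Deaths and life-threatening SAEs go to the main PI within 3 business days (7.8) and to RCHSPB Safety within 7 days (7.9.2).
- All SAEs arising at Asan go to the Asan IRB within one business day (7.9.3).
- SAEs arising at PNUH go to the PNUH IRB within 24 hours if fatal or potentially life-threatening, otherwise within 7 days (7.9.4).

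**Step 5: what remains.** Taking step 4 from step 3 leaves three exposures: the recording of non-serious events; the 7-day NIAID IRB route for non-fatal SAEs and unanticipated problems; and the NMC route.

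**The case against.** The strongest reply is that this is a drafting slip that no careful clinician would apply. Unrelated opens by requiring a clear absence of relationship, and what follows explains that judgment. The rest of 6.3 uses timing correctly, and 6.6.1 lists the anticipated single-dose reactions, including those to kanamycin and moxifloxacin. To do harm, a rater would have to call an event clearly unrelated because its timing fits, against everything else in the section. Much of this stands. It lowers the likelihood of misrating and so the severity. It does not make the clause right, and the clause sits in the scale that decides expedited reporting.

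A reader might infer three stronger points that the documents do not support.

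- *Drug reactions could drop out of safety reporting altogether.* Step 4 rules this out: SAEs are recorded whatever the rating, and several routes ignore relatedness. The move from 7 days to the annual summary concerns the NIAID IRB only.
- *Nearly every post-dose event is affected.* A reader might add the longest allowed interval from dose to ligation in section 3.3 (24 + 12 = 36 h) to the 48 h of follow-up after surgery, and conclude that every event falls within 84 h of dosing. That is not a maximum, because subjects outside the allowed windows are kept and analysed. Nor is it the capture period for grade 3 or 4 events, which ends with surgery. And an event that meets a stray clause has not thereby been misrated. Unlikely Related is already below the reporting threshold, so the fault matters only for an event that deserves Possibly or higher and is moved down on timing. The documents give no frequency for that.
- *Unrelated should require a documented alternative cause.* That would be a new rule, and it would override biological implausibility, which 6.3 accepts as a ground in its own right.

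**Conclusion.** The clause is wrong as written and should be fixed. It contradicts the causality principle and the three related categories of the section it stands in, and nothing elsewhere in the protocol corrects it.

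The size cannot be put as a number. The exposure is limited to non-serious events (grade 3 or 4 up to completion of surgery), 7-day NIAID IRB reporting of non-fatal SAEs and unanticipated problems, and NMC reporting framed on relatedness. The opening words of the category reduce the practical risk further. The primary endpoint, sample size and planned analyses are untouched.

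The conclusion rests on reading and/or in its ordinary sense, so that one ground can be enough, and on the assumption that sites rate events from the printed definitions.

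**What to change.** In the Unrelated definition in section 6.3, reconcile the time clause with the rest of the section by having it say that the temporal sequence is *not* consistent with study medication administration. Leave the other two grounds as they are.

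Send the corrected scale to the three sites. If any event has already been rated Unrelated on timing alone, re-check that rating and apply the reporting rule that follows from the result.

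The cost is one clause in an amendment, a notice to the sites and a short review of existing ratings, with perhaps a few more events recorded or reported within 7 days.

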## 6.4 Adverse Event Documentation

Any AE that will be reported on this trial will be fully and completely documented on the Adverse Event Case Report Form (CRF) and in the subject/study participant's clinical chart. The start date, the stop date, the severity of each reportable event, and the Investigator's judgment of the AEs relationship to the study agent/intervention will also be recorded on the CRF. In the event that the subject is withdrawn from the study due to an AE, it must be recorded on the CRF as such.

## 6.5 Adverse Event Treatment

Once an AE is known, staff at the study site should ensure that the subject receives prompt and appropriate care. Should a subject call a study clinician to report an AE, it will be determined at that time if an extra visit(s) will be scheduled, and/or appropriate medical advice will be provided. All actions taken by the investigator after observing an AE should be documented, including increased monitoring of the subject/study participant, suspension of the treatment, etc. Additionally, all calls will be documented in the subject/study participant's study chart, and discussed with the PI.

## 6.6 Potential Hazards

### 6.6.1 Anticipated Adverse Events

Each study drug will be administered only once, unless it is part of the subject's drug regimen prior to study initiation. Anticipated AEs related to a single dose of drug are as follows:

**RIF:** Orange staining of body fluids and GI upset.

**INH:** GI upset.

**PZA:** GI upset.

**KM:** Nephrotoxicity, vestibular toxicity ototoxicity (mostly with advanced age and prolonged use but possible with single dose) and local pain with IM injections,

**MXF:** Occasional GI intolerance, headache, insomnia, restlessness, dizziness and remote possibility of QT prolongation.

AEs and contraindications for all 5 study drugs can be found in “Drug-Resistant Tuberculosis: A Survival Guide for Clinicians.” [52]

Subjects will be monitored by the primary care team for these AEs. In women, the appearance of vaginal discharge will prompt a diagnostic work-up, or subjects will be empirically treated for Candida vaginitis.

## **7.7 Study Sites AE Reporting**

Since the subjects on this protocol will be seen because of illness, and are likely to be ill at baseline, many will have AEs by the above criteria. However, their medical management will be standard of care for those illnesses and complications and not part of the research process. Therefore, AEs associated with the underlying disease will not be recorded as AEs. However, AEs assessed to be related to the research will be recorded as such. As described below, all SAEs will be recorded and reported.

Any grade 3 or 4 AE (as defined in Section 7.1) that is possibly, probably or definitely related to study drugs and occurs between the times a subject signs the informed consent form and the time s/he completes the planned surgery (or at the time of early discontinuation of the subject from study participation for any reason) will be captured and recorded and reported with continuing annual review.

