### 3 Study Design and Methods

#### 3.1 Design

This is a single-dose pharmacokinetic study of 5 concomitant drugs where resected lung tissue will be recovered to determine and compare drug levels within plasma, sputum, healthy lung and pulmonary TB lesions over a 24h period. Comparison and modeling of the concentration-time profiles in plasma and lesions are used to infer permeability coefficients, exposure ratios and concentration gradients for five major 1st and 2nd line TB drugs: RIF, INH, PZA, KM and MXF. Subjects will be randomized to receive the 5 drugs at one time point, either at 2, 4, 8, 12 or 24h prior to surgery, or as close as practical to those times with careful recording of the time of administration. Enrollment will continue until evaluable tissues from 3 subjects have been processed at each assigned time point. Blood and sputum samples will be obtained just before drug administration (trough), and blood samples will also be obtained at 2h ( $C_{max}$ ) and 6h post-dosing or as practicable. Whenever possible, one additional blood and/or sputum sample will be obtained between drug dosing and surgery. Finally, blood will be collected at the time of central line placement and sputum at the time of intubation prior to surgery. The time of each blood draw and sputum collection will be recorded as carefully and accurately as possible. Urine will be systematically collected between the time of drug administration and surgery. The removed tissue will be dissected to separate lesion material from uninvolved lung. The location of each lesion within the lung lobes will be recorded. Each lesion will be measured and weighed, then further divided to perform the following analyses: determination of overall lesional drug concentrations by liquid chromatography-mass spectrometry (LCMS), imaging mass spectrometry and histopathology analyses to visualize 2D drug distribution within lesions. A pre-operative dynamic MRI scan (30-60 min duration) will be conducted one to two weeks prior to surgery to assess lesional perfusion and endothelial function. This procedure can be performed with most MRI machines in clinical use and this may be taken at a different site. A scan will be obtained before injection of the contrast agent (gadolinium). After the contrast agent is given, the subject will be scanned serially at several time points up to 8 minutes post-injection. The rate of gadolinium uptake and its retention properties will be determined using software. The entire scan will take about 45 minutes. A subject will participate in this study from entry (1 to 2 weeks prior to surgery), through surgery and for 48h post surgery.

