### **4.7 Study Completion**

A subject will have completed the study 48 hours post surgery (vessel ligation). If a subject withdraws or is withdrawn, for any reason, before lung tissue has been transferred to the dissection team, his/her participation in the study will be completed.

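### Capture of drug-related grade 3/4 adverse events closes at the end of surgery, although subjects stay on study until 48 hours afterwards

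*Protocol*

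**What the plan says.** Section 7.7 sets the only explicit window for non-serious events. A grade 3 or 4 event that is possibly, probably or definitely related to study drug is captured if it "occurs between the times a subject signs the informed consent form and the time s/he completes the planned surgery". A parenthesis gives the alternative end: "or at the time of early discontinuation of the subject from study participation for any reason".

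Two sentences in the same section carry no time limit: "However, AEs assessed to be related to the research will be recorded as such" and "As described below, all SAEs will be recorded and reported".

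Participation lasts longer than the window. Section 3.1 has the subject on study "through surgery and for 48h post surgery". Section 4.7 also puts completion at 48 h and names vessel ligation as the reference time.

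Section 4.6 withdraws, among others, subjects who do not have the operation and subjects without an evaluable primary endpoint. For a subject who withdraws or is withdrawn "before lung tissue has been transferred to the dissection team, his/her participation in the study will be completed", according to 4.7. Neither section makes an exception for someone already dosed.

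Section 6.6.1 lists renal, vestibular and ear toxicity for kanamycin, with the comment "mostly with advanced age and prolonged use but possible with single dose".

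**The concern.** The study stays open for 48 h after ligation, but the explicit rule for related grade 3/4 events stops at the end of the operation. The time line in 3.3.2 places no study procedure after surgery, so safety observation looks like the natural use of those 48 h. The one dated rule leaves that time out.

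A second gap concerns subjects who receive the five drugs and are then withdrawn, for example because the operation is cancelled. Participation ends on withdrawal, and the parenthesis in 7.7 closes capture at the same moment.

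At stake is the completeness of the record of non-serious, drug-related grade 3/4 events after a single dose. Sites also face two rules in one section and cannot tell which governs. The primary endpoint is untouched.

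**Working it through.** The protocol states no figure for post-dose observation time, so there is none to reproduce. The check is arithmetic on its own times.

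**Inputs**
- Nominal dose-to-ligation time *h*: 2, 4, 8, 12 or 24 h (3.3).
- Allowed deviations: −1/+3, −2/+4, −4/+6, ±6 and ±12 h respectively (3.3).
- Completion: 48 h after ligation (4.7).
- Planned group size: 3 evaluable subjects each (3.1, 3.3), so the groups are weighted equally.
- Time from ligation to the end of surgery: not given. Assumed 0 to 6 h.

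**Formulas**
- Post-dose time in the window, counted to ligation: *h*.
- Post-dose participation: *h* + 48.
- Share covered: *h* / (*h* + 48).

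| Group | In window (h) | Participation (h) | Share | Share over allowed deviations |
|---|---|---|---|---|
| 2 h | 2 | 50 | 4.0% | 2.0% (1 h) to 9.4% (5 h) |
| 4 h | 4 | 52 | 7.7% | 4.0% (2 h) to 14.3% (8 h) |
| 8 h | 8 | 56 | 14.3% | 7.7% (4 h) to 22.6% (14 h) |
| 12 h | 12 | 60 | 20.0% | 11.1% (6 h) to 27.3% (18 h) |
| 24 h | 24 | 72 | 33.3% | 20.0% (12 h) to 42.9% (36 h) |

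**Overall.** The mean time in the window is (2 + 4 + 8 + 12 + 24)/5 = 10 h. Mean participation is (50 + 52 + 56 + 60 + 72)/5 = 58 h. The share is 10/58 = 17%.

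**Allowing for surgery after ligation.** The window closes at the end of surgery, so the assumed lag is added to the 10 h:
- 2 h: 12/58 = 21%
- 4 h: 14/58 = 24%
- 6 h: 16/58 = 28%

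Between 72% (lag 6 h) and 83% (lag 0) of nominal post-dose study time therefore lies outside the explicit window.

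**With the window moved to completion.** Nominal capture after the dose becomes 50, 52, 56, 60 and 72 h, mean 58 h.

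**Early withdrawal.** Read together, 4.6, 4.7 and the parenthesis in 7.7 give a subject who is dosed and then withdrawn before tissue transfer no further time in the grade 3/4 window. No period after the dose is stated for such a subject.

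**The case against.** The strongest reply is that 7.7 does not rest on the dated sentence alone. It promises to record all serious events and all research-related events, with no cut-off at surgery. The serious-event clocks in 7.8 and 7.9 are not tied to the end of surgery and run mainly from awareness. Section 6.6.1 has the primary care team watch for the anticipated events with no end time. Section 6.5 covers events reported by telephone, and 7.9.3 and 7.9.5 require follow-up of reported events at two of the sites until they end.

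This stands for serious events, and the point does not extend to them. For non-serious grade 3/4 events it shows an open-ended rule beside a time-limited one, which is the conflict to be resolved.

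A reader might infer more than the protocol supports:
- **That drug toxicity is largely unobserved.** The undated sentences in 7.7 rule this out for serious events.
- **That kanamycin toxicity would mostly appear after the window.** No onset times are given. Section 10.3.2 calls every risk not in bold extremely unlikely after one dose, and the kanamycin risks are not in bold in the text available.
- **That observation differs twelve-fold between groups.** The ratio 24/2 stops at ligation. With surgery ending 2, 4 or 6 h later (assumed), it is 26/4 = 6.5, 28/6 = 4.7 or 30/8 = 3.75.
- **That events cannot be compared across groups.** Section 5.3 has no safety endpoint and 5.4 plans no such comparison.
- **That every dosed subject whose tissue is not transferred leaves at once.** Section 4.7 requires that the subject withdraw or be withdrawn.

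**Conclusion.** The mismatch holds in a narrow form. The explicit window for related grade 3/4 events closes at surgery or early discontinuation, while participation runs to 48 h after ligation. It covers about 17% of nominal post-dose study time counted to ligation, and 21 to 28% if surgery lasts 2 to 6 h beyond it. Those shares assume nominal dosing times and equal groups, and the time from ligation to the end of surgery is an assumption. They describe time under the rule, not a number of events missed, which the protocol gives no basis to estimate.

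The gap for dosed subjects withdrawn before tissue transfer also holds. Both are worth correcting because they affect participant safety data and the change is small. Neither bears on the permeability comparison or on the sample size.

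**What to change.** 1. In 7.7, replace the end-of-surgery limit with the study's own completion point, 48 h after vessel ligation. Use the same reference time in 3.1, which says only surgery.
2. In 7.7, reconcile the dated window with the two undated sentences. State which non-serious research-related events are recorded and until when, and when collection of serious events ends.
3. In 7.7 and 4.7, state that a subject who received study drug and is withdrawn early stays under adverse-event capture for a fixed period after the dose. The sponsor should choose the period. One option is to match the dose-to-completion interval of the other subjects, nominally 50 to 72 h.
4. While editing 7.7, correct its pointer for grading, which cites Section 7.1. Grading is in 6.2.

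The cost is a short amendment and slightly more adverse-event recording in about 15 patients who are already on study for those 48 h, plus a short observation period for any dosed subject withdrawn early.
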